## Abstract

**Background:**

Insomnia and work-related stress often co-occur. Both are associated with personal distress and diminished general functioning, as well as substantial socio-economic costs due to, for example, reduced productivity at the work place and absenteeism. Insomnia complaints by people experiencing work-related stress are correlated with a deficient cognitive detachment from work. Diffuse boundaries between work and private life can additionally complicate the use of recreational activities that facilitate cognitive detachment.

Cognitive behavioral therapy for insomnia is effective but rarely implemented. Internet-based cognitive behavioral therapy for insomnia could potentially reduce this deficit given its demonstrated effectiveness. Less is known, however, about the efficacy of internet-based cognitive behavioral therapy for insomnia in populations affected by high work stress. Thus, the aim of the present study is to evaluate the efficacy and cost-effectiveness of a newly developed, guided online training which is based on Cognitive Behavioral Therapy for insomnia and tailored to teachers affected by occupational stress.

**Methods/Design:**

In a two-arm randomized controlled trial (N = 128), the effects of a guided online sleep training will be compared to a waitlist-control condition. German teachers with significant clinical insomnia complaints (Insomnia Severity Index ≥15) and work-related rumination (Irritation Scale, subscale Cognitive Irritation ≥15) will be included in the study. The primary outcome measure will be insomnia severity. Additionally, an economic evaluation from a societal perspective will be conducted. Data from the intention-to-treat sample will be analyzed two and six months after randomization.

**Discussion:**

To the best of our knowledge, this is the first study to evaluate an online sleep training tailored to a specific population with work stress, that is, teachers. If this type of intervention is effective, it could reduce the paucity of cognitive behavioral therapy for insomnia and augment the support for teachers in coping with their insomnia problems.

**Trial registration:**

German Clinical Trial Register (DRKS):
DRKS00004700

## Background

Sleep and work represent areas of life in which the adult population spends most of their time. Not surprisingly, insomnia and work-related stress frequently co-occur and are interconnected
[1]. Stress at work may lead, for example, to a lower sleep quality and an increase in insomnia symptoms
[2-4]. In contrast, insomnia symptoms are negatively related to well-being at work and work pleasure
[5]. Chronic insomnia has a 10% prevalence rate in Western industrialized countries
[6,7], and 28% of Europeans suffer from work-related stress
[8]. Moreover, approximately one-third of the population in Germany suffers from frequent sleep problems
[9]. Insomnia and work stress are both associated with personal distress, diminished general functioning, increased absenteeism and presenteeism and, in turn, high personal and societal costs
[9-15].

Numerous studies have investigated the relationship between work stress and health impairments such as insomnia. For example, Akerstedt
[13] emphasized that a deficient recovery from work is one important risk factor for developing insomnia in people with work-related stress. Recovery can be defined as the process of psychophysiological unwinding after work, during which depleted resources are restored
[16]. Based on the allostatic load model
[17] and the effort-recovery model
[18], this psychophysiological unwinding is crucial for mental and physical well-being. Currently, recovery is well-recognized as an essential daily process to balance the strains of work
[19-21]. Cognitive detachment or ‘mentally switching off’ is a central determinant of recovery
[1,16,22], and it has been found to mediate the relationship between work stress and insomnia complaints
[23].

Cognitive detachment can be fostered by recreational activities
[19]. Moreover, a deficient cognitive detachment in the form of worrying and rumination on work-related problems can be reduced by interventions such as Cognitive Behavioral Therapy (CBT)
[24] or Metacognitive Therapy (MCT)
[25]. Ample evidence supports the efficacy of Cognitive Behavioral Therapy for Insomnia (CBT-I). Several meta-analyses, including Morin, Culbert and Schwartz (1994), showed large effect sizes for sleep onset latency and moderate effect sizes for quality of sleep and total sleep time experienced by adults with chronic primary insomnia (for example,
[26]). A meta-analysis by Smith *et al.* (2002) also illustrates that CBT-I is not only less risky with fewer adverse effects than pharmacological treatment, but also is more effective in the long term
[27].

However, the gap between the need for CBT-I and its availability and implementation is large
[28]. One reason for the deficiency in treatment might be that both patients and physicians often fail to recognize insomnia complaints as discrete symptoms requiring separate treatment. This neglect is problematic, given also that insomnia is a risk factor for other disorders such as depression
[29,30].

Internet-based CBT interventions have been shown to be effective for several health problems such as depression, anxiety, chronic pain and problem drinking, with an overall effect size of d = .52
[31] which is comparable to face-to-face psychotherapy
[32]. The effectiveness of iCBT-I has also been supported by strong evidence
[33,34]. In a recent meta-analysis
[33] significant effects were shown on sleep quality, sleep efficiency, number of awakenings, sleep onset latency and insomnia severity, ranging from moderate (for example, sleep quality) to large (insomnia severity) effect sizes. The underutilization of CBT-I could be potentially reduced by iCBT-I because of its several advantages such as its flexibility, broad availability and low threshold
[35].

However, less is known about the efficacy of iCBT-I in people affected by high work stress and even less in specific working populations such as teachers. Studies consistently report that 10 to 35% of teachers suffer from stress-related health issues such as exhaustion, depressive or somatoform symptoms
[36-39]. Moreover, teachers are more often affected by insomnia complaints than the general working population
[40]. Research on the particular stressful situation of teachers has led to calls for better prevention of mental health problems in the educational sector of Germany
[8]. Although the cost-effectiveness of internet-based CBT has shown promising results for several disorders
[41] such as depression
[42] or problem drinking
[43], the cost-effectiveness of iCBT-I interventions has not yet been investigated.

The planned trial, to our knowledge, is the first to evaluate an iCBT-I intervention that investigates the efficacy and cost-effectiveness of an iCBT-I intervention tailored to a specific population affected by work-related strain.

In the proposed randomized controlled trial, a guided self-help iCBT-I intervention tailored to school teachers affected by clinical significant insomnia symptoms and high occupational strain will be evaluated with regard to the reduction of insomnia severity. We hypothesize that the intervention will lead to reduced insomnia complaints and will be superior to a wait-list control condition in terms of cost-effectiveness.

## Methods/Design

### Study design

This study is a randomized controlled trial with the following two groups: an Internet-based guided self-help intervention group (GET.ON Recovery) and a wait-list control group (WL). The study will comprise an effectiveness study and an economic evaluation in parallel. The economic evaluation will be conducted from a societal perspective. Assessments will be taken at post-treatment (eight weeks) and in a six-month follow-up. The study has been approved by the Medical Ethics Committee of the Philipps University of Marburg (Nr.: 2013-01K).

### Inclusion and exclusion criteria

Inclusion criteria are: being a primary, secondary or vocational school teacher above the age of 18, currently in work and with significant clinical insomnia symptoms as measured by a score ≥15 on the Insomnia Severity Index (ISI)
[44] and work-related rumination as measured by a score ≥15 in the subscale ‘Cognitive Irritation’ of the Irritation Scale (IS)
[45], access to the Internet, an email address and a telephone number. Subjects receiving psychological help for their sleep problems or showing suicidal ideation will be excluded from participation. People taking sleep medication will not be excluded from the study. To screen for possible suicidal ideation and intentions, we will use item 9 from the Beck Depression Inventory II (BDI II)
[46] with scores of 0 (‘I don’t have any thoughts of harming myself’), 1 (‘I have thoughts of harming myself, but I would not carry them out’), 2 (‘I feel I would be better off dead’), and 3 (‘I would kill myself if I could’). Subjects scoring above the cut-off of 1 will be excluded from participation. We have a suicide protocol at place for those subjects who are excluded because of suicidal ideation. They will receive an email that refers them to their general practitioner and provides them with several telephone numbers and contacts that they can use to seek help.

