### Procedure

Participants will be recruited during March to June 2013 through email distribution lists by the ministry of education in the German state of Nordrhein-Westfalen (NRW). Principals of primary, secondary and vocational schools are invited to circulate a flyer to their teaching staff. Interested teachers can apply for participation by an email to the primary study investigator (first author). The primary study investigator will provide interested teachers with a PDF containing additional detailed information and a request to complete an online screening questionnaire, which will be available on the same homepage that will contain all other study questionnaires and the online training. Teachers will obtain access to the homepage by using their email address and a self-chosen password. We will provide eligible participants with an ID number and then ask them to a) provide informed consent, b) complete baseline questionnaires (including a 7-day sleep diary) and c) participate in a diagnostic interview via telephone. The diagnostic interview will take about 20 minutes and include sections from the Structured Clinical Interview for DSM-IV (SKID-I)
[47] and the Structured Interview for Sleep Disorders (SIS-D)
[48]. The diagnostic interview will not be used as an inclusion or exclusion measure but will provide diagnostic data for primary insomnia, major depression and generalized anxiety disorder. After the diagnostic interview, participants will be randomized. Assessments will occur at baseline, before randomization (T0), eight weeks post-treatment (T1) and six months follow-up (T2). We chose eight weeks for T1 as a post-treatment measure to ensure that all participants will have completed the six week training. Figure 
1 illustrates an overview of the procedures the participants will undergo.

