### Randomization

A computer program will automatically assign a 0 or 1 to each ID number, indicating the allocation to either the intervention or a waiting list. This random assignment is made in a 1:1 ratio.

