### Experimental condition

Participants in the intervention group will receive GET.ON Recovery after randomization. Participants in the control group receive GET.ON Recovery six months after randomization. Subjects of the control group will not be supported with feedback or reminders, but the primary study investigator will be available for questions concerning the content of the intervention or for technical problems.

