#### Screening

The ISI
[44], the ‘Cognitive Irritation’ subscale of the IS
[45], and item 9 of the BDI II
[46] will be administered as screening measures.

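### The suicide protocol and its referral email are tied to excluded people (BDI-II item 9 score 2 or 3); enrolled people who score 1 fall outside that stated trigger

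*Protocol article*

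**What the plan says.** The relevant text is in the protocol article under *Inclusion and exclusion criteria*. Suicidal ideation is named as a reason for exclusion, and item 9 of the BDI-II puts this into practice. The article prints all four answer levels; level 1 reads "I have thoughts of harming myself, but I would not carry them out". The rule is "Subjects scoring above the cut-off of 1 will be excluded from participation".

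The safeguard follows directly: "We have a suicide protocol at place for those subjects who are excluded because of suicidal ideation". The next sentence says what it consists of: "They will receive an email that refers them to their general practitioner and provides them with several telephone numbers and contacts".

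The *Screening* section names item 9 together with the ISI and the Cognitive Irritation subscale, which "will be administered as screening measures". Under *Procedure*, eligible people then have a telephone interview before randomization. It is not used to include or exclude anyone, but "will provide diagnostic data for primary insomnia, major depression and generalized anxiety disorder".

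**The concern.** The exclusion rule and the safety trigger share one cut-off, but they serve different purposes. The exclusion rule decides who may enter the trial. The email points a person who has disclosed a risk towards help. Placing the line between 1 and 2 is a defensible clinical choice for the first purpose. It does not follow that the same line is best for the second.

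Score 1 is a disclosure of self-harm thoughts, made in answer to a question that the trial itself asks. It is the only non-zero level that can be enrolled and the only non-zero level outside the stated trigger. At stake is whether someone who gives that answer is sent the help contacts that the trial already has ready. No estimate or test in the trial depends on it.

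**Working it through.** No arithmetic applies and the plan has no figure to reproduce. The check applies the stated rule to each answer level and then looks for any other provision in the article.

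**Step 1: apply the rule.** The levels are 0, 1, 2 and 3, and scores above 1 are excluded.

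| Item 9 score | Eligible on this criterion? | Within the stated suicide protocol and email? |
|---|---|---|
| 0 | yes | no (no ideation reported) |
| 1 | yes | no |
| 2 | no | yes |
| 3 | no | yes |

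The non-zero levels are 1, 2 and 3. The email is described for 2 and 3, which leaves level 1.

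**Step 2: check who receives the email.** The sentence on the suicide protocol names the people excluded for suicidal ideation. The sentence on the email takes them up with a pronoun and names nobody else. The scope is therefore stated in the text and is not inferred from an omission.

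**Step 3: look for a provision elsewhere in the article.**
- *Procedure:* the telephone interview collects diagnostic data, including on major depression. No safety action is attached to a finding.
- *Screening* and *Table 1:* item 9 is described as a screening measure, and Table 1 does not list it at T0, T1 or T2.
- *Depressive symptoms:* the ADS is a secondary outcome measured at T0, T1 and T2. No alert threshold is stated.
- *Support:* coaches answer questions, send reminders and give feedback on exercises and homework.
- *Experimental condition:* control participants can put questions about content or technical problems to the primary study investigator once they have the training. Safety is not mentioned.

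None of these sections extends the suicide protocol or the email to an enrolled person with score 1.

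**Step 4: check that a lower trigger is neutral between the arms.** Item 9 is answered at screening, and randomization comes only after the diagnostic interview. An email triggered by the screening score is therefore sent before allocation is known and reaches both arms by the same rule.

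**The case against.** The strongest objection is that a journal article condenses a fuller protocol. It mentions a suicide protocol without reproducing it, and the handling of low-level ideation in enrolled participants may well be set out there. The sentence also stands in a section on eligibility, where its natural task is to say what happens to people who are turned away. Enrolled people, unlike excluded ones, have further contact with the study: the telephone interview, the ADS at three time points and, in the intervention arm, a coach. The study also has ethics approval.

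Much of this stands. The article does not show that no procedure exists for score 1, and the fix has to be conditional on that. What does not fall away is that the article goes beyond silence: it says whom the suicide protocol is for and what is sent, and score 1 is not included. The further contacts carry no stated safety action.

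A reader might infer three stronger points, which the document does not support:
- *That enrolled people with score 1 receive no help contacts at all.* The text shows only that they are outside the stated trigger.
- *That the wait-list adds to the harm, because control participants receive the training only after six months.* The training is for insomnia and recovery and is nowhere described as care for suicidal ideation, so waiting for it withholds no such care. The one-in-two chance of waiting is the same for every participant.
- *That the cut-off is wrong because it admits people who report self-harm thoughts.* The article defines its exclusion by a score above 1 and prints every level, so the rule is clear, and its position is a clinical choice.

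**Conclusion.** The point holds as a minor participant-safety improvement. In the text shown, the suicide protocol and referral email are tied to people excluded with score 2 or 3, while people with score 1 can be enrolled and are outside that trigger.

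The size in people is unknown. The article gives no distribution of item 9 answers and no bound that would be informative. Counting answer levels shows where the gap lies, not how many people fall into it.

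The conclusion rests on reading the email's recipients as the excluded people of the sentence before, and on the full suicide protocol not already covering score 1. If it does cover score 1, nothing needs to change. The primary analysis and the power are not affected in either case.

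**What to change.** Keep the exclusion cut-off as it is. First check whether the full suicide protocol already provides for score 1. If it does not, send the existing referral email (general practitioner and help contacts) at screening to everyone who scores 1 or more on item 9, before randomization and regardless of later arm.

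The email already exists and the score is already collected, so the change is a lower trigger plus notice to the ethics committee. The downside is some additional emails and possibly some additional general practitioner visits. Those visits could occur in both arms and would be counted in the health care use recorded by the TiC-P. Eligibility, sample size and planned analyses stay unchanged.

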### Procedure

Participants will be recruited during March to June 2013 through email distribution lists by the ministry of education in the German state of Nordrhein-Westfalen (NRW). Principals of primary, secondary and vocational schools are invited to circulate a flyer to their teaching staff. Interested teachers can apply for participation by an email to the primary study investigator (first author). The primary study investigator will provide interested teachers with a PDF containing additional detailed information and a request to complete an online screening questionnaire, which will be available on the same homepage that will contain all other study questionnaires and the online training. Teachers will obtain access to the homepage by using their email address and a self-chosen password. We will provide eligible participants with an ID number and then ask them to a) provide informed consent, b) complete baseline questionnaires (including a 7-day sleep diary) and c) participate in a diagnostic interview via telephone. The diagnostic interview will take about 20 minutes and include sections from the Structured Clinical Interview for DSM-IV (SKID-I)
[47] and the Structured Interview for Sleep Disorders (SIS-D)
[48]. The diagnostic interview will not be used as an inclusion or exclusion measure but will provide diagnostic data for primary insomnia, major depression and generalized anxiety disorder. After the diagnostic interview, participants will be randomized. Assessments will occur at baseline, before randomization (T0), eight weeks post-treatment (T1) and six months follow-up (T2). We chose eight weeks for T1 as a post-treatment measure to ensure that all participants will have completed the six week training. Figure 
1 illustrates an overview of the procedures the participants will undergo.

**Figure 1 F1:**
[figure not shown]
**Research procedure.** Subjects interested in participation receive online screening questionnaires. Eligible subjects then are asked to sign informed consent, fill in the baseline questionnaires and take part in a diagnostic interview via telephone. After that, subjects are randomized into either intervention or control group. Further assessments take place two and six months after randomization. Subjects of the control group get access to the intervention (self-help) following the last assessment.

### Randomization

A computer program will automatically assign a 0 or 1 to each ID number, indicating the allocation to either the intervention or a waiting list. This random assignment is made in a 1:1 ratio.

### Sample size

The sample size will be based on the difference between experimental and control group at post-test on the primary outcome measure (insomnia severity). We expect a difference of Cohen’s d = .50. Given an alpha of .05 and 1 - beta = .80 in a two-tailed test, we will need 64 subjects in each condition with a total sample size of N = 128. Based on a recent meta-analysis on the efficacy of online insomnia trials
[33], we could expect a higher effect size (d = .86) for our primary outcome. But our target group differs from the group assessed in the meta-analysis, thus we chose a rather conservative estimate to reduce the chance of an under-powered study.

### Intervention

The online recovery training for better sleep (GET.ON Recovery) is a newly developed iCBT-I training, which uses well-established CBT-I methods such as sleep restriction, stimulus control, sleep hygiene and cognitive interventions
[49]. These methods are supplemented by techniques from behavioral activation, MCT
[50] and gratitude research
[51].

The theoretical assumption underpinning GET.ON Recovery is that the participants’ insomnia symptoms are caused and maintained by an impaired or even missing recovery from their daily work-related effort. Thus, symptoms will improve if their recovery is enhanced during the night (better sleep through sleep hygiene, stimulus control and sleep restriction) and at the weekend (better cognitive detachment from work-related problems through recreational activities, and through worry and rumination techniques)
[26,52].

The intervention consists of six one-week sessions. In the first session, participants will receive information about recovery (that is, how sleep, cognitive detachment and recreational activities are interconnected), and they will be educated on sleep hygiene. In session two, participants will learn why stimulus control and sleep restriction are effective methods to overcome sleep problems. Participants will be asked to plan the first step in sleep restriction and accordingly reschedule their sleep for the following week. In session three, participants will review their progress on sleep restriction and sleep hygiene and then schedule their sleep for the next week according to their sleep restriction plan. Then they will be presented with ‘boundary tactics’
[53], which are practical behaviors that help to clearly distinguish work and private life. The session will end with an exercise on the gratitude journal, a well-studied method on how to end the day and to improve sleep
[51]. In sessions four and five, participants will be provided with psycho-education about worrying and rumination and how it influences sleep. Different exercises will be presented, all aimed at fostering the ability to become more cognitively detached from work-related problems, and in turn reduce worrying and rumination. The fifth session is based on MCT
[54], which is grounded in the assumption that enduring attention on thoughts can further increase their frequency and intensity. Participants will learn two MCT exercises: detached mindfulness and attention training.

In every session, homework will be given to help participants actively plan and implement recreational activities into daily life according to the behavioral activation approach. Additionally, participants will be asked to choose one exercise from the session to apply throughout the forthcoming week. The intervention will conclude with a ‘relapse-prevention’ session (session six) that summarizes what will have happened in the preceding five sessions. This session will provide an opportunity for participants to reflect and elaborate on their progress and future goals. Additionally, participants will choose exercises from the preceding five sessions that they believe will help prevent relapse (when sleep gets significantly worse).

